#### Practical applicability

3.3.2

The communication strategy for disseminating trial results to participants and Air Force professionals involves presenting comprehensive data collection information, results, and conclusions to the Health and Exercise Department of the Portuguese Air Force. This initiative holds particular significance as there is currently no established formal exercise program for training aircraft pilots. The outcomes of this study may prove instrumental in the creation or enhancement of such a program, thereby contributing to the improvement of future military health policy.

For the broader public and other pertinent groups, access to the study’s findings can be facilitated through publication in scientific journals. This dissemination approach ensures that the study’s outcomes are accessible to a wider audience, contributing to the broader scientific and professional knowledge base.

#### Arms and intervention

3.3.3

Table 1 outlines the study arms: the control group receiving military training alone and the intervention group undergoing both military training and yoga classes.

**Table 1 tab1:** Arms and assigned interventions of the study protocol.

Arms	Assigned interventions
Experimental: Yoga	Yoga practice: 12-week program of Ashtanga Vinyasa Yoga Supta for 1 h twice a week; other names – yoga class
No Intervention: Waiting list	Exclusively compulsory training (the same for all academy attendees).

The yoga practice, as depicted in Image 2, entails fluid sequences (Ashtanga Vinyasa Yoga) performed with closed eyes (supta) to address perceived difficulties in pilots. The yoga classes comprise five main components:5 min of prathyáhara (abstraction)—“withdrawal of the senses” or “sensory withdrawal,” involves consciously detaching the senses from external stimuli and directing attention inward. Through pratyahara, practitioners aim to disengage from external distractions, facilitating a deeper exploration of the inner self and enhancing self-awareness.5 min of pranayama (breathwork, including raja pranayama and kryia)—these are advanced forms of breathwork aimed at regulating the breath and influencing the flow of prana (life force energy) throughout the body. Raja Pranayama focuses on controlling the breath through various breath retention methods, such as inhaling (puraka), holding the breath (kumbhaka), and exhaling (rechaka) in specific ratios. Kriya pranayama techniques typically combine specific breath control, body postures, and mental focus to influence the flow of prana (life force energy) throughout the body. Nauli Kriya is an advanced yogic purification technique that involves isolating and rhythmically churning the abdominal muscles. It is performed by contracting and rolling the abdominal muscles in a specific manner to create a rolling or rippling motion across the abdomen.35 min of ásana (physical postures)—with sun salutations, as depicted in Image 3 and sequenced physical postures, as depicted in Image 4, involving spinal flexion, extension, lateral flexion, rotation, and inversions, changes in head positioning entailing a recalibration involving the integration of visual, vestibular, and muscular sensations, combined with breath control and abstraction, for a holistic approach to health and well-being.5 min of dhāraṇā (practice of concentration or single-pointed focus)—beginning with yoga nidra for physiological relaxation, followed by mental exercises to focus and prepare for meditation. Yoga nidra is the practice of deep relaxation or yogic sleep. It is a state of consciousness between wakefulness and sleep, where the body and mind are in a state of profound rest while remaining fully aware. During yoga nidra, practitioners typically lie down in a comfortable position and follow guided instructions to systematically relax different parts of the body, release tension, and enter a state of deep relaxation. The practice often involves techniques such as body scanning, breath awareness, visualization, and mindfulness. Dhāraṇā involves directing one’s attention to a specific object, thought, or sensation, and maintaining that focus without distraction. This object of focus could be anything, such as a physical object, a mental image, a mantra, or the breath. The goal of dhāraṇā is to develop greater mental discipline, control over the wandering mind, and the ability to sustain attention for prolonged periods.5 min of dhyána (meditation or contemplation)—involves focused concentration and sustained attention on an object, thought, or sensation to achieve a state of mental clarity, stillness, and inner awareness. During dhyana, practitioners aim to quiet the mind, transcend distractions, and cultivate a deep sense of presence and mindfulness, focused on developing greater mental resilience and emotional balance. Sankalpa (“resolve” or “intention”) was also used during meditation, it is a tool used to set a clear and positive intention for one’s life or practice, a heartfelt affirmation of one’s deepest values, aspirations, and purpose. It serves as a constant reminder of what truly matters and empowers individuals to align their thoughts, words, and deeds with their deepest intentions.

**IMAGE 2 fig2:**
[figure not shown]
AVYSM classes structure and components.

**IMAGE 3 fig3:**
[figure not shown]
Sun salutations (28) used in the ásana component of the AVYSM classes.

**IMAGE 4 fig4:**
[figure not shown]
Various yoga postures (ásanas) incorporated in the ásana component of the AVYSM classes.

The components will be adapted to the specific needs of the pilot group during their flight missions: supta classes, primarily or entirely conducted with closed eyes, aim to eliminate visual system responses and evoke vestibular system responses; Ashtanga Vinyasa classes emphasize fluid movement sequences, focusing on breathing and enhancing neck and upper limb strength through various yogic movements available to the head and spine (flexion, extension, lateral flexion, rotation, and inversion). This recalibration facilitates the pilot’s awareness of their spatial orientation, complemented by improvements in embodiment and proprioception. This, in turn, enhances the pilot’s perception of the aircraft’s orientation and their own position in relation to it, as well as their spatial awareness of the aircraft in relation to the Earth. The classes will commence with basic-level techniques, progressing to more advanced ones as the intervention group’s proficiency and abilities improve over the timeline.

#### Statistical analysis

3.3.4

Sample size was calculated with OpenEpi. Data analyses will be done with MATLAB (18) and Jamovi (29), based on the type of data; analyses will be performed based on the underlying assumptions for parametric, or non-parametric testing. In detail, for all difference testing, data and variance distribution (i.e., normality) will be checked. The alpha-error threshold is set at 5%, all *p* values below are considered significant.

For the primary outcomes related with postural control and heart rate variability a MATLAB (18) routine will be used to treat data exported from the Biosignals Plux platform and also from the Polar H10 portable monitor, and with those values a Shapiro–Wilk normality test will be performed and either a T-test for paired samples will be applied on parametric data or a Wilcoxon rank test will be applied on non-parametric data.

For the primary outcomes related with operative performance and the secondary outcomes a Shapiro–Wilk normality test will be performed and either a T-test for paired samples will be applied on parametric data or a Wilcoxon rank test will be applied on non-parametric data.

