### Study design, ethics approval and informed consent publication

3.1

The study was approved by the Évora University Research Ethics Committee, with approval number 21050, and participants gave written informed consent. The study is in agreement with the Declaration of Helsinki. The trial was registered in ClinicalTrials.gov with identifier NCT05821270, registered on 19th April 2023. Furthermore, this intervention protocol was accepted by the PAto be applied on Airbase 11 in Beja. A randomized, prospective, controlled two-arm trial will be adopted, in which one arm will be the control group (waiting list) and the other the intervention group (yoga).

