#### Sample size determination

3.2.1

Among all military personnel in the Portuguese Air Force, the inclusion criteria for participation in this study comprise healthy individuals serving as military pilots actively engaged in their training (tirocinium) at the PAA, which consists of taking the course titled “Masters in Military Aeronautics: Aviator Pilot Specialist.”

Conversely, the exclusion criteria encompass military pilots on active duty either preceding (not aviation pilots yet) or following the tirocinium (distributed by different airbases inside and outside the country and flying different types of aircrafts in restricted, classified or warzones), those with injuries, and individuals undergoing sudden lifestyle changes (e.g., initiating or discontinuing smoking habits, commencing, or ceasing any form of medication, or adopting a new diet).

There are currently 19 pilots actively undergoing their training (tirocinium) at the PAA, serving within “Esquadra 101 - RONCOS,” situated at Airbase 11 in Beja, which comprises the totality of this population for the PA. These pilots are divided into two classes, and they share common aircrafts, specifically the Aerospatiale Epsilon TB-30. Additionally, both classes are assigned comparable workloads and operational tasks.

Within these criteria there are 19 individuals serving as military pilots actively engaged in their training (tirocinium) at the PAA, specifically within the PA course titled “Masters in Military Aeronautics: Aviator Pilot Specialist,” and our sample size is calculated with OpenEpi, with a 95% confidence interval, which corresponds to 19 subjects—the totality of this population, as seen in Image 1.

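### A low-power Shapiro–Wilk result chooses the test for every outcome, so the test behind each p value is fixed only after the data are seen and may differ between arms

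*Protocol article*

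**What the plan says.** Section 3.3.4 (Statistical analysis) states the selection rule twice.

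- **HRV and postural control.** After the MATLAB routine has processed the exported recordings, "with those values a Shapiro–Wilk normality test will be performed and either a T-test for paired samples will be applied on parametric data"; a Wilcoxon test is used on data judged non-parametric.
- **Operative performance and all secondary outcomes.** "For the primary outcomes related with operative performance and the secondary outcomes a Shapiro–Wilk normality test will be performed", followed by the same choice of two tests. This sentence does not name the quantity that is checked.

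A general sentence above both says that "for all difference testing, data and variance distribution (i.e., normality) will be checked". Significance is judged at 5%.

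On size, section 3.2.1 says: "There are currently 19 pilots actively undergoing their training (tirocinium) at the PAA". Section 3.1 says: "A randomized, prospective, controlled two-arm trial will be adopted". Neither section 3.1 nor section 3.2.3 (Randomization procedure and blinding) gives an allocation ratio. Section 3.3.4 does not say whether the check is run per arm, per visit or on all pilots together.

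**The concern.** The rule makes the test for each outcome depend on a preliminary test in the same small sample. Three features make it a weak rule here.

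1. **Low power.** With about 9 or 10 values, Shapiro–Wilk often passes data that are clearly skewed. A pass is then little evidence that the t-test is suitable.
2. **The quantity checked.** A paired t-test relies on normality of the within-pilot differences. Pilots can differ from one another in a skewed way while their changes are normal, and the reverse. No sentence names the differences, and for HRV and postural control the wording points to the processed values.
3. **No single answer.** If the check is made separately in each arm, one arm can pass and the other fail. The rule then gives different tests for one outcome, or leaves the choice open.

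At stake is whether the analysis of the primary outcomes is settled before the data are seen. Near the 5% line the verdict can depend on which test the gate picked, and the results are meant to inform Air Force training policy (sections 3.3.2 and 4).

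**Working it through.** **The plan's own figure.** Section 3.2.1 reports that "our sample size is calculated with OpenEpi, with a 95% confidence interval, which corresponds to 19 subjects". The finite-population formula for a proportion is n = N·p·q / [(d²/z²)(N − 1) + p·q]. N = 19 and the 95% level are stated. The anticipated frequency p = 0.5 and precision d = 0.05 are assumptions, because the figure that may show them is not available. Then n = 19 × 0.25 / [(0.0025/3.84) × 18 + 0.25] = 4.75 / 0.2617 = 18.15, rounded up to 19. The stated size is reproduced, and nothing below changes it.

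**Inputs.** The documents give a total of 19, two arms and a 5% level (taken as two-sided). Arm sizes of 9 and 10 assume near-equal allocation and full enrolment. The distributions are assumptions, because the protocol gives no standard deviations or shapes.

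**Step 1: how often Shapiro–Wilk rejects normality at 5%** (simulation)

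| True distribution | n = 9 | n = 10 | n = 19 |
|---|---|---|---|
| Normal | 5% | 5% | 5% |
| t, 5 df | 11% | 11% | 18% |
| Lognormal, sigma 0.5 | 22% | 24% | 50% |
| Lognormal, sigma 0.8 | 41% | 47% | 81% |
| Exponential | 39% | 44% | 81% |
| Lognormal, sigma 1 | 54% | 60% | 92% |
| Poisson count, mean 2 | 25% | 29% | 56% |

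The last row matters because section 2.1 includes the number of errors in the emergency protocol among the primary outcomes. That is known to be a count before any data are collected, yet with a mean of 2 it would pass as normal in about 75% of samples of 9.

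**Step 2: chance that the two arms get different tests.** This assumes one check per arm. With rejection rates a (n = 9) and b (n = 10), the chance is a(1 − b) + b(1 − a).

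- Normal: 0.050 × 0.947 + 0.053 × 0.950 = 0.098, about 10%.
- Lognormal 0.5: 0.215 × 0.757 + 0.243 × 0.785 = 0.354, about 35%.
- Lognormal 0.8: 0.41 × 0.53 + 0.47 × 0.59 = 0.495, about 49%.
- Lognormal 1: 0.543 × 0.397 + 0.603 × 0.457 = 0.491, about 49%.

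**Step 3: checking values against checking differences.** Pilot levels were simulated as lognormal (sigma 0.5 to 1) with exactly normal changes. Checking the baseline and follow-up values rejected normality in 21–61% of samples of 9 or 10; checking the differences rejected in about 5%. The two checks disagreed in 24–60%. This step bears on the plan only where the values are what is checked.

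**Step 4: does the verdict depend on the choice?** Paired t and Wilcoxon signed-rank tests were compared at n = 9 with a true mean change of 0.9 SD. They fell on opposite sides of 0.05 in 8% of samples with normal changes, 9% with skewed levels and normal changes, and 9% with lognormal (sigma 0.8) changes. The figure moves with the assumed shape and effect.

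**Step 5: error rates of the two-stage rule.** In paired null cases with no mean change, gating on the values gave a type I error of 0.038–0.048. With skewed levels, normal changes and a real effect, gating on the values gave power 0.63 against 0.66 for the t-test used throughout. With skewed changes it gave 0.95 against more than 0.99 for the signed-rank test.

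**The case against.** The strongest reply is that the text does not say what a critic may read into it, and that the practical damage is small.

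- **Which quantity is checked.** A reader might infer that normality is checked on the measured values and not on the differences for every outcome. The documents do not support that. The wording points to the values only for HRV and postural control, and even there it is the natural reading rather than an explicit statement. For all other outcomes the quantity is unnamed, and the general sentence ties the check to difference testing. Nothing excludes a check on the differences, and a separate analysis plan could specify it. This stands, so step 3 is conditional.
- **Chosen by chance.** A reader might call the choice of test random. That goes too far: for strong skew (lognormal, sigma 1) the check detects the departure in 54–60% of samples.
- **False positives.** A reader might expect an inflated type I error. The simulations show none due to the gate. In one strongly skewed null setting the two-stage rule rejected in 12%, but the ungated t-test (13%) and signed-rank test (10%) behaved alike, so the gate is not the cause.
- **Size of the disagreement.** In a two-sample comparison of 9 against 10 with lognormal (sigma 0.8) data, t and rank tests disagree in about 18% of trials. The plan specifies paired tests, for which the figure is about 9%.
- **Arm sizes and per-arm checking.** Both are assumptions. Participation is voluntary (section 3.2.2) and no allocation ratio is given.
- **Variance equated with normality.** The phrase "data and variance distribution (i.e., normality) will be checked" is loose wording and changes no analysis.

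What the reply does not remove is the gate itself. The article states it twice, so it is not a detail left to a fuller document. Naming the differences as the quantity checked would settle step 3, but not the low power or the possible mismatch between arms.

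**Conclusion.** The point holds in this form. For every primary and secondary outcome the test is chosen by a Shapiro–Wilk result that, at about 9 or 10 pilots per arm, detects lognormal skew in about 22–24% (sigma 0.5) to 41–47% (sigma 0.8) of samples. The plan does not specify that the within-pilot differences are what is checked. If the check is made per arm, the arms get different tests in about 10% (normal) to 35–50% (lognormal) of outcomes, and in roughly 9% of samples with a real effect the choice decides significance.

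The validity of the 5% level is not threatened by the gate, and the loss of power is usually a few points. The harm is that the test is settled only after the data are seen and may not be comparable across arms. This makes it a worthwhile, inexpensive improvement rather than a flaw that invalidates the trial. The sizes rest on near-equal allocation, full enrolment, a per-arm check and assumed distributions.

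**What to change.** Delete the Shapiro–Wilk gate from section 3.3.4 and name one test per outcome before the data are seen. The preferred choice is a permutation test between arms of the baseline-adjusted 12-week value, for continuous and count outcomes alike, reported with an estimate and an interval. It needs no normality assumption and suits a design that aims to randomise all 19 eligible pilots. Use residual plots for description only, never to select the test.

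The permutations must follow the actual allocation scheme. Section 3.2.3 names the random-number service but not the ratio or any restriction, so state these too. If the arms were fixed at 9 and 10 without further restriction, there would be 19!/(9!·10!) = 92,378 possible allocations, few enough to enumerate completely.

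This remedy also moves the contrast from within pilots to between arms. If the within-pilot contrast is kept for any outcome, naming one paired test for it in advance would still answer this point.

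**Cost.** About two sentences and a short script in the MATLAB already in use, plus one sentence on the allocation scheme. If a rank version is chosen and the data are normal, a few points of power are lost: in the simulated 9-against-10 comparison with a shift of 1, power was 0.49 for the rank test and 0.54 for the t-test.

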### Primary outcomes

2.1

Changes in Operative performance—Flight times to complete tasks in the flight simulator; number of errors during the emergency protocol and their classification report from the flight simulator controller (12). The assessment will determine if the exercise protocol influences the pilot’s decision-making, as evidenced by improved task efficiency, reduced errors, and enhanced visual and auditory reaction times (1, 2)—Time Frame: measured at 12 weeks (vs. baseline values).

Changes in Stress and HRV—Heart rate variability, measured with Polar H10 portable device (2, 13–15). The assessment will reveal if the exercise protocol influences pilots’ responses to stressors, with a lower stress response enhancing decision-making (4)—Time Frame: measured at 12 weeks (vs. baseline values).

Changes in Vestibular system control responses—The Center of Pressure (CoP) represents the dynamics of the neuromusculoskeletal system, was measured with a portable force plate (Biosignals Plux-Portugal) with a sample frequency at 1000 hz. and data downsampled to 100 Hz (16, 17). Preprocessing performed using the EEGLAB toolbox, which is available for use in MATLAB (The MathWorks Inc., Natick, MA) (18). Enhanced postural control responses may indicate the protocol’s potential to mitigate the effects of spatial disorientation (6, 7)—Time Frame: measured at 12 weeks (vs. baseline values).

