## Results

4

The principal objective of the study is to assess the feasibility and efficacy of implementing a 12-week yoga program to enhance existing military training protocols within the Portuguese Air Force. This will be accomplished through the utilization of a randomized controlled intervention design. The intervention comprises preventive exercises tailored to address perceived challenges faced by pilots during aircraft piloting, thereby enhancing the capabilities of individuals who are already undergoing training.

The findings of this study hold significance for the research group and are equally pertinent for policymakers within the Portuguese Air Force. The data gathered in this project can aid policy makers in developing a tailored exercise regimen.

Broadening the study’s relevance to diverse contexts, the methods, results, and discussions generated by this project have the potential to be extrapolated to diverse military contexts, beyond military aviation, exploring applications of human intervention in different military settings, such as incorporating new training techniques for: airfield operations officers, paratroopers, armored vehicle operators, tank crews, navy divers, military paratroopers, and others, where the improvement of physical and cognitive abilities aligns with the outcomes of this study. Furthermore, the applicability of the project’s findings extends to high-demand environments beyond military, including civil aviation (both for pilots and air traffic controllers), professional race car or motorcycle drivers and skydiving companies—professions where the optimization of physical and cognitive capabilities may offer valuable insights and benefits.

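### Only paired before-after tests are specified for every outcome of this randomised two-arm trial; no comparison of yoga with waiting list is prespecified

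*Protocol article*

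**What the plan says.** The protocol article, section 3.1, sets the design: "A randomized, prospective, controlled two-arm trial will be adopted", with a waiting list as control. Section 4 (Results) states the objective as feasibility and efficacy of the yoga programme and adds: "This will be accomplished through the utilization of a randomized controlled intervention design".

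Section 3.3.4 then fixes the tests in two parallel paragraphs. One begins "For the primary outcomes related with postural control and heart rate variability a MATLAB (18) routine will be used to treat data" and the other "For the primary outcomes related with operative performance and the secondary outcomes a Shapiro–Wilk normality test will be performed". Together they cover all three primary outcomes and all secondary outcomes. Both end with the same rule: Shapiro–Wilk, then either "a T-test for paired samples will be applied on parametric data or a Wilcoxon rank test will be applied on non-parametric data". The alpha level is 5%.

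The primary outcomes (section 2.1) are changes, each with the contrast "Time Frame: measured at 12 weeks (vs. baseline values"). The secondary outcomes (section 2.2) carry the same time frame. Table 1 says that the waiting-list arm receives only the compulsory training, which is the same for everyone at the academy.

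**The concern.** A paired-samples test asks whether the mean change from baseline is zero in the pilots it is applied to. It does not ask whether the change is larger with yoga than without, which is the question that the randomisation was set up to answer.

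The distinction matters in this setting. The participants are trainee pilots in an active flying course. The first primary outcome is simulator task time and errors in the emergency protocol, measured twice, 12 weeks apart. Improvement through training and familiarity with the test is plausible in both arms, and the waiting list is there to remove it. If the stated tests carry the inference, two misreadings are open: a significant change in the yoga arm taken as a yoga effect, or significance in yoga together with non-significance in control taken as a difference between arms. Neither holds the 5% error rate when both arms improve. The article intends the results to inform Air Force training policy and to be extended to other occupations, so a false attribution would have consequences.

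**Working it through.** **1. The plan's own figure.** The only statistical figure besides alpha is the OpenEpi sample size of 19. The formula for a frequency in a finite population is n = N·p(1−p) / [(d²/z²)(N−1) + p(1−p)]. With N = 19 and z = 1.96, and assuming p = 0.5 and d = 0.05 because the image is not shown:

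n = 4.75 / (0.0117 + 0.25) = 18.15, rounded up to 19.

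The figure reproduces (d = 0.10 would give 17). It is a survey-precision calculation with no effect size, power or arm contrast, so it does not show that a between-arm comparison was planned.

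**2. What the named tests can estimate.** Each pilot contributes a baseline and a 12-week value and sits in one arm. The article describes no matching of pilots across arms. The only pairs are therefore before and after in the same pilot. Whether the test is run in each arm or pooled over both, it estimates a mean change and not a difference between arms. An independent-samples test, a comparison of changes between arms, a group-by-time term or a baseline-adjusted model is named nowhere in the article.

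**3. Illustration with no yoga effect.** The documents give neither the allocation split nor the size of any learning effect. The following are assumptions:
- 10 yoga and 9 control pilots, from the total of 19
- common gain g of 0.3, 0.5 or 0.8 SD of the outcome in both arms
- pre-post correlation r of 0.5 or 0.7
- normal data and two-sided tests at the stated 5%

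The SD of change is √(2(1−r)), which is 1.000 for r = 0.5 and 0.775 for r = 0.7. The standardised common gain is L = g / √(2(1−r)). The chance that a paired t-test with n pilots is significant comes from the noncentral t distribution with n−1 degrees of freedom and noncentrality L√n. The arms are independent, so the chance of significance in yoga only is P(yoga) × (1 − P(control)).

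| g | r | L | P(yoga significant), n=10 | P(control significant), n=9 | Yoga only |
|---|---|---|---|---|---|
| 0.3 | 0.5 | 0.300 | 13.6% | 12.5% | 11.9% |
| 0.3 | 0.7 | 0.387 | 19.5% | 17.7% | 16.1% |
| 0.5 | 0.5 | 0.500 | 29.3% | 26.3% | 21.6% |
| 0.5 | 0.7 | 0.645 | 44.6% | 40.0% | 26.8% |
| 0.8 | 0.5 | 0.800 | 61.6% | 55.9% | 27.2% |
| 0.8 | 0.7 | 1.033 | 82.7% | 77.4% | 18.7% |

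For the row with g = 0.5 and r = 0.5, for example, 0.293 × (1 − 0.263) = 0.216.

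**4. The same trials with a between-arm test.** A two-sample t-test on the changes has a null distribution that does not depend on the common gain. In 100,000 simulated trials at each of L = 0, 0.5, 0.8 and 1.0 it rejected in 5.0% of trials. With no common gain (L = 0), the yoga arm's paired test also rejects at 5%, so the excess comes entirely from change shared by both arms.

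**The case against.** The best defence is that this is a condensed article, that section 3.3.4 speaks generally of difference testing, and that nothing in it rules out a comparison of the arms. This stands in part. A reader might infer that the arms will never be compared, or that randomisation is wasted. The text does not support that: it specifies no such comparison, which is not the same as excluding one, and it does not say that a p-value from the yoga arm alone will be called a yoga effect. The defence does not remove the point, however. The article does not defer the choice of test. It names one for every outcome, and that test does not estimate the randomised contrast.

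It can also be said that the Wilcoxon test might be the rank-sum version, which does compare groups. It is offered as the alternative to a paired t-test, so signed-rank is the natural reading. Even on the other reading, the parametric branch has no between-arm test.

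The inflated error rates rest on an assumed common gain, and no learning effect is given in the documents. This is fair. Shared improvement is most plausible for operative performance. The article gives no particular reason to expect it for spirometry, body composition or SF-36.

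Finally, a reader might infer from "with those values a Shapiro–Wilk normality test will be performed" that normality will be checked on raw values instead of paired differences, or arm by arm, so that the two arms could receive different tests. The section says neither. The values meant may simply be the output of the MATLAB routine, and a check by arm is not mentioned. No part of this point relies on that inference.

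**Conclusion.** The analysis is wrong as written. For every primary and secondary outcome the specified test is a within-person comparison over time, while the stated design and objective call for a comparison of randomised arms. That conclusion follows from the text alone and needs no numerical assumption.

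The size of the possible error does need assumptions. With 10 versus 9 pilots, no yoga effect, a common gain of 0.3 to 0.8 SD and a correlation of 0.5 to 0.7, a significant paired result in the yoga arm occurs in about 14% to 83% of trials, and the pattern of significance in yoga only in about 12% to 27%, against 5% for a between-arm test. These figures are conditional illustrations. They do not predict what this trial will show.

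**What to change.** Rewrite section 3.3.4 so that a between-arm comparison is the inferential analysis for each outcome:
- Fit a linear model of the 12-week value on arm and baseline value, and report the adjusted difference with a 95% CI. A two-sample test of change would also hold the 5% level.
- For skewed outcomes and error counts, use a rank-based or permutation test of the arm difference. A permutation test must follow the allocation scheme actually used, so the ratio and method of allocation need to be stated. Adjustment for pilot class is optional.
- Analyse pilots in the arm to which they were assigned.
- Report within-arm paired changes as description only.

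No new data are needed, since baseline and 12-week values are already part of the plan. The abstract describes allocation and the control period in the past tense, so data may already exist. In that case the change should be recorded as a dated amendment to the analysis.

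The change restores validity but not precision. With 10 versus 9 pilots, a two-sample t-test on change has 18% power for a difference of 0.5 SD of change, 38% for 0.8 and 54% for 1.0, and reaches 80% only at about 1.37. The confidence interval should therefore carry the interpretation.
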